## **8.2 Severity**

The physician will use the following definitions to rate the severity for any adverse event being collected as an endpoint/data point in the study and for all serious adverse events.

- |                  |                                                                                                                                       |
|------------------|---------------------------------------------------------------------------------------------------------------------------------------|
| Mild:     | The adverse event is transient and easily tolerated by the subject.                                                                   |
| Moderate: | The adverse event causes the subject discomfort and interrupts the subject's usual activities.                                        |
| Severe:   | The adverse event causes considerable interference with the subject's usual activities and may be incapacitating or life threatening. |

## **8.3 Relationship to Pharmaceutical Product**

The investigator will use the following definitions to assess the relationship of the adverse event to the use of study drug:

- |                                  |                                                                                                                            |
|----------------------------------|----------------------------------------------------------------------------------------------------------------------------|
| Reasonable Possibility    | An adverse event where there is evidence to suggest a causal relationship between the study drug and the adverse event.    |
| No Reasonable Possibility | An adverse event where there is no evidence to suggest a causal relationship between the study drug and the adverse event. |

If an investigator's opinion of no reasonable possibility of being related to study drug is given, an alternate etiology must be provided by the investigator for the adverse event.

## **8.4 Serious Adverse Event Collection Period**

Serious adverse events will be reported to Abbott from the time the physician obtains the patient's authorization to use and disclose information (or the patient's informed consent) until 30 days following the intake of the last dose of physician-prescribed treatment.

[figure not shown]

## 8.5 Serious Adverse Event Reporting

In the event of a serious adverse event, the physician will:

- For events from patients using and Abbott product - notify the Abbott contact person identified below within 24 hours of the physician becoming aware of the event.

Contact information of Abbott representatives:

## **8.6 Pregnancy Reporting**

Information regarding a pregnancy occurrence in a study subject and the outcome of the pregnancy will be collected.

Pregnancy in a study subject is not considered an adverse event. However, any complication of pregnancy, (such as elective or spontaneous abortion, stillbirth, congenital anomaly etc.) is considered a serious adverse event and must be reported to Abbott within 24 hours of the site becoming aware of the event.

In the event of a pregnancy occurrence in the patient, the physician will notify the Abbott contact person identified in Section 8.5 within 24 hours of the physician becoming aware of the pregnancy.

## **9.0 Ethics and Quality**

Patient's written authorization to use and/or disclose personal and/or health data must be obtained prior to enrolling each patient in the program and patients not willing to provide such written authorization will not be included in the program. However, all reasonable efforts will be made in order to avoid subject identifying information (such as name, address, etc).

**Russia:** the protocol and relevant program documents will be submitted for review and approval of Regulatory Authorities and Central and/or local (if applicable) Independent Ethics Committee(s) (IEC) and patient enrollment will start only after obtaining written approval from the IEC.

**Ukraine:** the protocol and relevant study documents will be submitted for review and approval to State Expert Center of Ministry of Health of Ukraine by Abbott. It is the responsibility of each investigator to obtain study approval (if applicable) of Local IEC before initiating the study, if applicable.

[figure not shown]

All data will be captured and handled in such a way so as to not reveal identity of individual patients and hence patient confidentiality will be maintained at all times.

The physician/investigator will be responsible for ensuring that a quality control and quality assurance system is in place to ensure that the program is conducted and data generated, documented, and reported in compliance with the protocol, accepted standards of Good Clinical Practice, and any applicable local laws and regulations.

The Abbott representative can monitor the case report forms after completion in EDC. Any discrepancies will be communicated to site for clarification. Any necessary corrections will be made to the database per applicable EDC procedures.

## **10.0 Case Report Forms**

For this program electronic Case report forms (eCRF) will be used. eCRF will be completed for each subject enrolled in this program. These forms will be used to transmit and collect the program data for Abbott (or a CRO for data management) and regulatory authorities, as applicable. Electronic CRFs will be set by Abbott designee as web based site. All eCRFs must be legible and data must be entered by trained and authorized person only. eCRF training will be performed for site staff during site initiation. eCRF tracks all changes to the entered data automatically. Data discrepancies detected by eCRF will be addressed to investigator. All information entered in the eCRFs must also be reflected in the subject source documents.

The investigator will store subject data in his/her source documents in accordance to his/her praxis routine. These subject files will serve as source data for the program. The principal investigator will review the eCRFs for completeness and accuracy and sign each subject's set of eCRFs by electronic signature where indicated. The eCRFs will be reviewed periodically for completeness, legibility and acceptability by Abbott personnel (or their representatives).

[figure not shown]

## 11.0 Data Analysis Plans

### General Principles

The principal features of the statistical analysis of the data are described in this section. Since this is an open-label, non-randomized trial, the analyses will primarily involve the generation of descriptive summary statistics. Quantitative variables will be summarized with number of patients, mean, standard deviation, median, 1st quartile, 3rd quartile, minimum and maximum values. Qualitative variables will be summarized with the number and proportion of patients in each category. In addition, two-sided 95% confidence intervals will be generated for parameter estimates. Graphs may be generated for visual interpretation of the results, as appropriate.

### Data Analysis Set

**All Patients Set** will include all patients who signed patient authorization form to participate in the study. This population will be used for presenting disposition of subjects.

**Full Analysis Set** will include those patients who attended Visit 1 and who were administered at least one dose of betahistine dihydrochloride (Betaserc®), as assessed in the CRF. This population will be used for the reporting of effectiveness results.

### Summary of Demographic and Baseline Characteristics

Demographic and baseline characteristics will be summarized with descriptive statistics described above and presented for total study population as well as for each involved country – Russia and Ukraine.

- Age will be summarised with number of patients, mean, standard deviation, median, 1st quartile, 3rd quartile, minimum and maximum values. Proportion of patient with age greater or less and equal to median will be presented.

[figure not shown]

- Sex and race will be summarized with number and proportion of patients in each category.
- Weight and height will be used for calculation of body mass index. Body mass index will be summarised with number of patients, mean, standard deviation, median, 1st quartile, 3rd quartile, minimum and maximum values.
- Findings of concomitant medication will be summarized with number and proportion of patients in each category.
- Findings of medical history will be summarized with number and proportion of patients in each category.
- Findings of physical examination will be summarized with number and proportion of patients in each category. Heart rate, blood pressure (systolic and diastolic), will be summarised with number of patients, mean, standard deviation, median, 1st quartile, 3rd quartile, minimum and maximum values. Proportion of patients with potentially clinically significant vital signs findings will be summarized with number and proportion of patients in each category.

Criteria for identifying potentially clinically significant vital signs findings presented below:

Criteria for Identifying Potentially Clinically Significant Vital Signs Findings

| Variable (units) |                                 | Range |     |
|------------------|---------------------------------|-------|-----|
| Blood Pressure   | Systolic Blood Pressure (mmHg)  | 80    | 160 |
|                  | Diastolic Blood Pressure (mmHg) | 50    | 100 |
| Heart rate (bpm) |                                 | 40    | 150 |

- Specific underlying ICD-10 diagnosis account for Vestibular Vertigo will be summarized with number and proportion of patients in each category.

[figure not shown]

### **Analysis of Primary Endpoint**

1. Number and proportion of patients with clinical response at the end of observational treatment period that is determined based on the SVVSLCRE. The normal approximation two-sided 95% confidence interval for binominal proportion will be generated.

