## **7.2 Number of Patients to be Enrolled**

A total of 310 patients will be enrolled in this program from approximately 10-35 centers in Russia and Ukraine.

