### **Sample size considerations**

Based on evaluation of literature data that was published by Gananca et al. in *Acta Oto-Laryngologica*, 2009 [17], proportion of patients with Meniere's Disease achieved control of vertigo (clinical conditions levels 4 and 3) after 12 weeks of treatment with betahistine dihydrochloride tablets constituted 88%. Benecke et al. [18] found that overall efficacy of betahistine in routine clinical practice over 3 months therapy was excellent by 36.6% of 1753 patients with recorded data (n = 641) and good by 49.6% of patients (n = 870), total 86.2 %. The investigators' impression of the treatment was excellent for 38.6% of patients (n = 675 of 1747) and good for 50.5% of patients (n = 883), total 89.1%.

For this program, it is assumed that at least 80% of the total study sample will achieve clinical response after 60 days of therapy with betahistine dihydrochloride tablets. When the sample size without a consideration of dropout is 246, a normal approximation two-sided 95% confidence interval for a single proportion using normal distribution will extend 5.0% (i.e. half width of the 95% confidence interval) from the observed proportion for an expected proportion of 80% [19; 20]. Considering an approximate dropout rate about 20%, total study population (received at least one dose of betahistine dihydrochloride (Betaseron®) tablets and have at least one post-baseline assessment) will constitute 308 patients.

Overall, the best consideration for total number of enrolled patients with vestibular vertigo in the program has to amount 310.

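### The normal-approximation interval fixed for the primary response proportion covers slightly less than 95% at the response rates the protocol quotes, and its misses fall mostly on a lower limit set too high

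*Protocol*

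**What the plan says.** The only analysis specified for the primary endpoint is the number and proportion of responders with an interval (Protocol, section 11.0, Analysis of Primary Endpoint): "The normal approximation two-sided 95% confidence interval for binominal proportion will be generated". No continuity correction or other type of interval is mentioned.

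The study is sized on the same interval (Protocol, section 11.0, Sample size considerations). The planning rate is stated as "it is assumed that at least 80% of the total study sample will achieve clinical response after 60 days of therapy". The precision statement begins "When the sample size without a consideration of dropout is 246" and says that the interval "will extend 5.0% (i.e. half width of the 95% confidence interval) from the observed proportion for an expected proportion of 80" per cent. With about 20% dropout this "will constitute 308 patients", and section 7.2 rounds up: "A total of 310 patients will be enrolled in this program". The same section supports the planning rate with published results of 88%, 86.2% and 89.1%.

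General Principles in section 11.0 describes the analyses as mainly descriptive. No null value, success threshold or target for the lower limit is given anywhere.

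**The concern.** The Wald interval centres on the observed proportion and takes its standard error from that same proportion. When the true rate is well above one half, a sample that happens to come out high also gets a standard error that is too small, so its lower limit can end up above the truth. Samples that come out low get a wider interval and miss less often. The result is coverage a little under the label and an imbalance between the two tails.

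The protocol expects rates in this region. In a single-arm programme without a control, the lower limit is what a reader takes as the smallest response rate the data support, and this is the limit the method tends to set too high.

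**Working it through.** **Inputs, all from the Protocol**
- Two-sided 95% normal-approximation interval (section 11.0, Analysis of Primary Endpoint), z = 1.96.
- Rates p = 0.80 (planning), 0.862, 0.88 and 0.891 (published results cited under Sample size considerations).
- n = 246 (before dropout), 308 (after 20% dropout) and 310 (section 7.2). Effectiveness is reported on the Full Analysis Set, so the number analysed may lie anywhere from about 246 to 310.

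**Step 1: the plan's own figures**
- n = z² p(1−p)/0.05² = 3.8415 × 0.16/0.0025 = 245.85, so 246.
- Half-width at 246: 1.96 × √(0.16/246) = 0.04999, or 5.0 points.
- 246/0.80 = 307.5, so 308, rounded up to 310.

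All three reproduce. The sample size is right for the method named.

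**Step 2: exact coverage**

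For each n and p, the binomial probabilities of all outcomes x = 0, …, n whose interval contains p are added up. Misses are split into lower limit above p and upper limit below p.

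Wald: p̂ ± z√(p̂(1−p̂)/n).

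Wilson: [p̂ + z²/2n ± z√(p̂(1−p̂)/n + z²/4n²)] / (1 + z²/n).

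Wald coverage at the protocol's rates:

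| n | 80% | 86.2% | 88% | 89.1% |
|---|---|---|---|---|
| 246 | 94.0% | 94.5% | 94.8% | 94.3% |
| 308 | 94.2% | 93.6% | 93.9% | 93.9% |
| 310 | 94.3% | 94.4% | 94.1% | 94.7% |

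All twelve values are below 95%.

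Averages over a fine grid of true rates from 80% to 90%, for n = 246, 308 and 310:

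| Interval | Coverage | Lower limit too high | Upper limit too low |
|---|---|---|---|
| Wald | 94.4% to 94.6% | 3.7% to 3.9% | 1.7% |
| Wilson | 95.0% | 2.1% to 2.2% | 2.8% |

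On this grid Wald coverage runs from a minimum of 93.0% to 93.3%, depending on n, up to 95.5%. It reaches 95% at 17% to 19% of the rates. The lower-limit error is the larger one at every rate on the grid.

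**Step 3: effect on the reported limits, n = 310**

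| Responders | Observed | Wald | Wilson | Lower limit, Wald minus Wilson |
|---|---|---|---|---|
| 248 | 80.0% | 75.5% to 84.5% | 75.2% to 84.1% | 0.4 point |
| 273 | 88.1% | 84.5% to 91.7% | 84.0% to 91.2% | 0.5 point |

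Differences are taken before rounding (75.55 − 75.19 = 0.36; 84.46 − 83.98 = 0.48).

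**Step 4: what Wilson does to the planned precision**

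At n = 246 and p̂ = 0.80, z²/n = 0.01562.
- Centre: (0.80 + 0.00781)/1.01562 = 0.7954.
- Half the total width: 0.0498, or 4.98 points.
- Limits: 74.56% and 84.52%, that is 5.44 points below and 4.52 points above the estimate.

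The total width is practically that of the Wald interval, but it no longer extends an equal distance on each side.

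**The case against.** The protocol names a standard interval in advance, sizes the study on the same interval and gets the arithmetic right. At about 250 to 310 patients, preferring another interval is a choice between accepted methods. The average shortfall is about half a percentage point, and nothing in the protocol turns on a lower limit that moves by as little. Wilson is not better at every rate: over 80% to 90% it is itself below 95% at 47% to 48% of rates. At n = 310 it gives 94.5% against Wald 94.3% at a true 80%, and 94.5% against 94.7% at 89.1%.

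All of this stands, and it sets the weight of the point. It does not remove it. Wilson has the right coverage on average, and its remaining imbalance is smaller and leans the cautious way.

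Four stronger readings may tempt a reader, and the document does not support them:
- That the Wald interval falls short of 95% at every high response rate. Because the binomial is discrete, some rates between 80% and 90% reach it.
- That the shortfall should be judged at response rates above those quoted, where it can be larger. The highest rate in the protocol is 89.1%.
- That the same interval carries into the diagnosis, sex and country subgroups. The protocol states no subgroup sizes and leaves the methods for these exploratory analyses to the statistical analysis plan, which is not at hand.
- That the sample size is wrong. It is not.

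**Conclusion.** The point holds as a minor one about the primary interval only. At the protocol's own rates and sample sizes, an interval labelled 95% covers 93.6% to 94.8%, and it errs about twice as often by setting the lower limit too high as by setting the upper limit too low. In practice the reported lower limit would be about 0.4 to 0.5 point higher than the Wilson limit at 310 patients. No stated decision or conclusion changes.

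This rests on a binomial model with independent patients, on true rates of 80% to 90%, and on an analysed number of 246 to 310.

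**What to change.** Two edits in section 11.0 of the Protocol, made together:
- **Analysis of Primary Endpoint:** name the Wilson score two-sided 95% interval instead of the normal approximation.
- **Sample size considerations:** name the same interval and restate the 5.0% as half the total interval width at an expected 80% with 246 patients (4.98 points for Wilson; about 5.4 points below and 4.5 above the estimate). Changing only the first place would leave this sentence describing a symmetric interval that is no longer used.

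The figures 246, 308 and 310 stay as they are. The cost is a software option, one reworded sentence, and an interval that cannot be reported as estimate plus or minus a single margin.

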### **Secondary Endpoints**

Analysis of secondary endpoints will be done only for supporting evidence without any intention for a claim of treatment benefit for the secondary endpoints. Therefore, p-values and confidence intervals for secondary endpoints are purely for descriptive purposes and not for drawing inferences.

1. Number and proportion of patients in each category of SVVSLCRE at baseline and the end of observational treatment period will be presented for patients who completed betahistine treatment over a period less or equal 30 days and for patients who completed betahistine treatment over a period more than 30 days but less or equal 60 days.
2. Change of the patient's clinical conditions of vestibular vertigo assessed with SVVSLCRE from baseline to the end of observational treatment period will be presented with median, 1st quartile and 3rd quartile. Comparison between baseline and the end of observational treatment period will be made using Wilcoxon signed-rank test for dependent variables. Test statistic and p-value will be presented for each comparison. Tests resulting in p-values less than or equal to 0.05 will be reported as "statistically significant".
3. Change of the patient's clinical conditions of vestibular vertigo assessed with SVVSLCRE from baseline to Visit 2 will be presented with median, 1st quartile and 3rd quartile. Comparison between baseline and Visit 2 will be made using Wilcoxon signed-rank test for dependent variables. Test statistic and p-value will be presented for each comparison. Tests resulting in p-values less than or equal to 0.05 will be reported as "statistically significant".

[figure not shown]

4. Change of vestibular vertigo attacks frequency in number of monthly attacks from baseline to the end of observational treatment period will be summarized with number of patients, mean, standard deviation, median, 1st quartile, 3rd quartile, minimum and maximum values. Descriptive statistics will be also presented for each measure at baseline and the end of observational treatment period. Comparisons of the measures between baseline and the end of observational treatment period will be performed using the two-tailed paired t-test for dependent samples (if the data have approximate normal distribution) or a Wilcoxon signed-rank test for dependent variables (a nonparametric test). Test statistic and p-value will be presented for each comparison. Tests resulting in p-values less than or equal to 0.05 will be reported as "statistically significant".
5. Change of vestibular vertigo attacks frequency in number of monthly attacks from baseline to Visit 2 will be summarized with number of patients, mean, standard deviation, median, 1st quartile, 3rd quartile, minimum and maximum values. Descriptive statistics will be also presented for each measure at baseline and the end of observational treatment period. Comparisons of the measures between baseline and the Visit 2 will be performed using the two-tailed paired t-test for dependent samples (if the data have approximate normal distribution) or a Wilcoxon signed-rank test for dependent variables (a nonparametric test). Test statistic and p-value will be presented for each comparison. Tests resulting in p-values less than or equal to 0.05 will be reported as "statistically significant".
6. Overall clinical response assessed by physicians based on a four-point scale will be presented with number and proportion of patients in each category at the end of observational treatment period for patients who completed betahistine treatment over a period less or equal 30 days and at Visit 2 and 3 for patients who completed betahistine treatment over a period more than 30 days but less or equal 60 days.

[figure not shown]

7. Overall clinical response assessed by patients based on a four-point scale will be presented with number and proportion of subjects in each category at the end of observational treatment period for patients who completed betahistine treatment over a period less or equal 30 days and at Visit 2 and 3 for patients who completed betahistine treatment over a period more than 30 days but less or equal 60 days.
8. Clinical response as improvement of vertigo associated symptoms (tinnitus, hearing loss, nausea, vomiting, faintness and headache) and evaluated by physicians based on a four-point scale will be presented with number and proportion of patients in each category at the end of observational treatment period for patients who completed betahistine treatment over a period less or equal 30 days and at Visit 2 and 3 for patients who completed betahistine treatment over a period more than 30 days but less or equal 60 days.
9. Clinical response as improvement of vertigo associated symptoms (tinnitus, hearing loss, nausea, vomiting, faintness and headache) and evaluated by patients based on a four-point scale will be presented with number and proportion of subjects in each category at the end of observational treatment period for patients who completed betahistine treatment over a period less or equal 30 days and at Visit 2 and 3 for patients who completed betahistine treatment over a period more than 30 days but less or equal 60 days.
10. Change of vestibular vertigo attacks frequency in number of monthly attacks from the end of observational treatment period to 1st month of follow-up and from the end of observational treatment period to 2nd month of follow-up will be presented for patients who completed betahistine treatment over a period less or equal 30 days and for patients who completed betahistine treatment over a period more than 30 days but less or equal 60 days and will be summarized with number of patients, mean, standard deviation, median, 1st quartile, 3rd quartile, minimum and maximum values. Descriptive statistics will be
-

[figure not shown]

also presented for each measure at the end of observational treatment period, 1st month of follow-up and 2nd month of follow-up. Comparisons of the measures between the end of observational treatment period and 1st month of follow-up and between the end of observational treatment period and 2nd month of follow-up will be performed using the two-tailed paired t-test for dependent samples (if the data have approximate normal distribution) or a Wilcoxon signed-rank test for dependent variables (a nonparametric test). Test statistic and p-value will be presented for each comparison. Tests resulting in p-values less than or equal to 0.05 will be reported as "statistically significant".

11. Specific underlying ICD-10 diagnosis account for Vestibular Vertigo will be summarized with number and proportion of patients in each category.

